### 5.3. Participant follow-up

Participant will not be required for further follow up after the 6 week study period. However, participant are encouraged to be in contact with the research team if they would like to share their experience past the study (i.e. felt better with light, effect lasted longer than 6 weeks etc..). We will contact participants at the end of the study to inform them about the study outcomes.

### 5.4. Data collection

Participants medical history and medication will be recorded. As outlined in the HREA form (Q3.5), we will also collect qualitative (i.e. from questionnaires sleep, mood, quality of life) and quantitative (i.e. vision and motor function and salivary melatonin levels) data.

### 5.5. Data collection/gathering techniques:

1. Questionnaires for screening: Three validated questionnaires will be used to screen the PD participants stage of disease using the Movement Disorders Society Unified Parkinson's Disease Rating Scale (MDS-UPDRS), the Hoehn & Yahr scale to determine PD stage and severity and the Addenbrooke's Cognitive Examination (ACE) (score <82) for exclusion of dementia. We will also determine the participants chronotype using the Morningness Eveningness Questionnaire (MEQ), so the timing of the individual supplemental light intervention can be personalized (morning or evening light exposure).

Questionnaires at every lab visit: Participants will complete five additional validated questionnaires; the Pittsburgh Sleep quality index (PSQI), the Epworth Sleep Scale (EES), the Parkinson's Disease Sleep Scale (PDSS) to assess sleep behaviour, the Parkinson's Disease Questionnaire (PDQ-39) and the Beck's Depression Inventory-II to assess quality of life and mood, respectively. Participants will also complete a sleep diary to record sleep behaviour and subjectively determine sleep efficiency over 6 weeks. We have used this protocol including PSQI, ESS and sleep diary successfully in people with PD and in patients with diabetes.

2. As part of the screening, we will assess the health of the eye as per established ophthalmological examination (i.e. visual acuity, eye pressure, slit lamp, funduscopy, optical coherence tomography) performed in every clinic.
3. We will use pupillography, a device to measure the pupil diameter in response to a light stimulus to determine melanopsin cell function as per established standards and used in our laboratory in PD as well as diabetes and retinal/optic nerve diseases (i.e. current low risk QUT HREC approval no 1700000699). For measuring the pupil, the participant will place their head on a chin rest (similar to that used in an ophthalmic or optometric eye exam) and a short duration (1s) light stimulus will be directed towards the right eye whereas the other eye's pupil movements will be measured via an infrared camera and then analysed as per our established procedures in the laboratory.
4. To determine the dark (sleep) hormone melatonin and the circadian phase, we use established procedures for dim light melatonin (DLMO) determination and as used in our current research (i.e. low risk QUT HREC approval 1700000699). Participants will provide salivary samples by chewing a cotton swab for 1min. They

are asked to spit the saliva swab in the pre-labelled tubes (salivettes) provided by the researcher. The participant will provide saliva every hour, starting 6 hrs prior to their sleep time and one more sample after ~ 1hr in bed. With permission, to prevent the participant from missing a sample collection, an hourly reminder will be given through phone call or text messages. Participants can store the samples in their fridge and a research team member will collect them the next day, or if applicable, the participant will bring them to their laboratory visit the next day. Melatonin concentration determination will be outsourced and performed at the Adelaide Research Assay Facility as previously used in our studies.

5. Polysomnography (PSG) is an established sleep test in PD and will be measured at home at the participants own convenience, before and after 4 weeks of the supplemental light exposure and the following two weeks without supplemental light exposure (to determine the duration of effect of light exposure, “wash out”). It non-invasively records, through sensors attached to i.e. the head, arm, chest and legs, information used to evaluate sleep staging, eye and limb movement. A member of the research team will place the sensors on the participant on completion of the first laboratory visit in order to measure sleep functions during the night before the start of the light intervention. The research staff will visit the participant’s home the next morning to remove the sensors. After four weeks of light intervention, the research staff will return to the participant’s home in the afternoon and places the sensors for the second (post-intervention) polysomnography sleep test. Sensors will be removed the next day on their second laboratory visit. Two week later the researcher will return to the participants home to set up sensors for the final PSG to determine the long-term effects of supplemental light exposure (see 7.7 schedule of measurements in **Table 1** above). Sleep data analysis and training of research team members in analysis will be performed by [name] who is an accredited sleep physician.
6. Established tests for motor assessment will be applied in addition to the MDS-UPDRS. The positive effect of light on motor function is less clear in PD and is thought to be influenced by the changes in melatonin secretion patterns from the pineal gland. Moreover, improved motor function due to “sleep benefit” is attributed to increased dopamine storage during sleep. In addition, our research demonstrated that deep brain stimulation of areas central to sleep (pedunculopontine nucleus) can improve gait. Both gait and balance measures are established methods for determining motor function in PD and with which we have extensive experience.  
 Gait: Participants will walk at their own pace for 2 trials on a firm surface with bare feet. Walking will be recorded using a ProtoKinetics pressure sensitive matt that records temporospatial parameters of gait (e.g. velocity, stride length, stride time variability and cadence). Upper body motion (i.e. medio-lateral) and arm swing will be recorded using inertial sensors. These parameters are established as important indicators of dynamic postural stability during locomotion in PD.  
 Balance & Tremor: These will be assessed utilizing methods previously established by our group. Standing balance will be assessed on a force plate (100Hz) on a firm and a foam surface with eyes open and closed (4 trials of 30s). Force plate centre of pressure in the medio-lateral and anterior-posterior direction provides an objective measure of postural stability. Tremor assessment will be undertaken with arms relaxed by participant’s side (for resting tremor) and while holding arms out in front (postural tremor); accelerometers are placed on the left and right fingers to record movement. Tremor will be quantified from the accelerometer signals in the time and frequency domain using our previously established methods. Tremor assessment contributes to objective determination of Parkinson’s sub types (Tremor; Akinetic Rigid; Mixed) relative to those derived from MDS-UPDRS ratings.
7. We will use established actigraphy methods (i.e. Geneactive) to measure the environmental light exposure and activity as previously used in our studies. Participants are asked to wear this watch-like device over the period of the study (6 weeks).

#### 5.6. **Impact of and response to missing data e.g. extrapolation; participant withdrawal**

Our statistical methods also allow for a 15 % drop out rate in case some of the participants cannot be retained. We can also extend our recruitment period to longer than 18 months and recruit more participants if required.

#### 5.7. **Safety and adverse effects/events**

The proposed experiments are considered low risk because there is a low probability of slight inconvenience, but no harm to the participant associated with the research.

1. There might be slight inconvenience in answering many questionnaires and breaks will be given. Participants can choose to do some of these questionnaires at home at their own convenience. They can also choose not to answer questions without negative consequence.
2. All ophthalmic examinations to assess the front and the back of the eye involve shining a light into the eye. These are standard clinical tests applied in clinical practice and may incur slight inconvenience due to a

bright light exposure. However, the procedure is done within a few minutes and the participant can choose to have a break between the examinations.

3. Pupillometry, a test that measures the pupil in response to light and dark may incur slight inconvenience due to the exposure of a bright light. This light exposure occurs only for 1s per measurement (in total 4 measurement) and breaks will be given in between the measurements. The light levels used during the experiments are comparable to, or lower than levels commonly encountered outside on a sunny day. Standard optical corrections ensure that there is no risk of eye damage from ultra-violet light (UV: short wavelength between ~290 - 400 nm), sometimes called the blue light hazard. We use an optical system which provides a non-invasive method to present carefully controlled coloured lights to the eye. The pupil size is simultaneously recorded using an infra-red camera. These are standard procedures for the measurement of visual function and pupil control ([name], Cao, Morris & Zele, 2011, *Investigative Ophthalmology & Visual Science*, 52(2), 1145-1150; Zele, Maynard & [name], 2013, *Journal of vision*, 13(1), 1-19; Joyce, [name] & Zele, 2016, *Investigative Ophthalmology & Visual Science*, 57(13), 5672-5680). These low risk methodologies have been approved previously by the QUT HREC (e.g., #1400000842, #1500000468, #1400000543, and #1300000089, #1800000843).
4. Collection of saliva samples is non-invasive and will be used solely for melatonin measurement and not for any other purpose. There might be slight inconvenience in chewing on a cotton swab (in particular when having a dry mouth) and participant are allowed/ encouraged to drink water beforehand to ease this inconvenience if it occurs.  
Researchers are aware of infection control principles when handling saliva samples provided by the participant. Samples are collected by participant and not the researcher which minimizes the risk of cross-contamination. Participants provide the sample in a sealed biohazard bag.  
Appropriate PPE (i.e. gloves) and washing facilities are provided for the researcher.  
The researcher has a good understanding of the 'pathway' in the unlikely scenario they are exposed to bodily fluids. Researchers involved in saliva pick up for the participant's home are educated in the area of infection control/prevention.
5. A commercially available ambulatory polysomnography system will be used (Somte PSG). Polysomnography is used successfully in children and adults with and without PD. There might be a slight inconvenience having sensors attached to the skin overnight. However, they will be professionally placed on the skin and will not negatively impact on sleep.
6. Motor function assessment. There is a minor risk of a falling when testing gait and balance motor functions in participants with PD, however all the assessments will be closely monitored by research staff. The motor function assessment has been approved by our low risk QUT HREC#1700000005.
7. Supplemental bright light therapy is a safe treatment used in many sleep and neurological disorders including in Parkinson's disease. A recent systematic review of 77 studies using supplemental light therapy in different disorders (i.e. sleep disorders, seasonal affective disorders, depression) demonstrated no severe safety concerns. However, bright light exposure may cause short-lived and mild discomfort such as headache and eye strain that subsides after the light is discontinued. Another meta-analysis of 6 randomised controlled studies (RCT) using light in bipolar disorder also reported no severe side effects. The most common adverse effects were very rare and are listed below:

headache = 4.7% (7/148)  
sleep disturbance = 1.4% (2/148)  
insomnia = 0.68% (1/148)  
eyestrain = 0.68% (1/148)  
fatigue = 0.68% (1/148)  
dizziness = 0.68% (1/148)  
state of confusion and sedation = 0.68% (1/148)  
nightmares = 0.76% (1/132)  
nausea = 0.76% (1/132)  
palpitation = 0.76% (1/132)  
irritability = 0.76% (1/132)

If a participant complains about any of the above symptoms during or after light therapy the research team will discuss them with the participants, and dependent on the severity, can advise withdrawal from the study. The supplemental light source built in our QUT laboratory is safe from any blue light hazard, with a light level lower than commonly experienced outdoors on a sunny day. The output light levels are similar to those generated by commercially available light boxes used for supplemental bright light therapy.

8. Light therapy: Safety information and risk management:

The light box will come with explicit instructions for use, which will disallow any action other than connecting power and turning it on/off.

The light box is powered by a low voltage (up to 24V 4A or equivalent) power pack supplied by an Australian distributor, which will comply with national safety standards. There are small charge-holding components (inductors) in the unit which discharge within a few milliseconds of the power supply being turned off. There may be a coin cell battery inside the unit. Heat-dissipating components are appropriately heatsinked which minimises the possibility of component failure. In the unlikely event that an electrical component fails during operation, current will be stopped by a fuse or an open-circuit failure condition, in addition to the safety measures required of the power pack. The circuitry is located inside the unit which further reduces the possibility of contact with a current-conducting component. Moreover, the unit is highly unlikely to catch fire because it is made of non-combustible materials (primarily acrylic and plastic). If the unit does fail for any reason, the participant is instructed to turn off the unit at the wall, unplug, and inform investigators for replacement.

In an instance that a participant disregards the user instructions, the unit is designed and constructed so as to make accessing the internal electronics extremely difficult. Opening the light box will make the unit unfit for purpose and will be discouraged. Bare electrical wiring and connection points will be protected to limit the possibility of bridging different voltages.

The output light levels are safe and comparable to, or lower than, levels commonly encountered outside on a sunny day. Standard optical corrections ensure that there is no risk of eye damage from ultra-violet light (i.e. no blue light hazard). If the optical components fail, they do not emit light (rather than emitting additional light). The light boxes will be tested for electrical and optical faults before being given to participants.

9. The Actiwatch is a commercially available wrist worn device, no bigger than a standard watch and should not cause any discomfort during wear. It may cause slight inconvenience as it should be worn day and night and only removed when showering.

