## Endpoints

### Primary

- Change from baseline to week 4 and week 6 in mean objective sleep macrostructure (polysomnography, PSG): Sleep stages (N1, N2, N3, REM), Total sleep time, Sleep onset latency, Stage REM latency, Sleep efficiency, Time awake, Total PLMS Arousal Index
- Change from baseline to week 4 and week 6 in mean DLMO decimal time

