#### Dim Light Melatonin Onset (DLMO)

At each time point, seven saliva samples were collected in separate tubes (Salivettes, Sarstedt AG & Co, Adelaide, Australia) under dim light illumination ( $<30 \text{ lux}$ ) every hour starting 6 hours before habitual bedtime and ~ 1 hour

after bedtime at the participant's home. Participants were asked to write the time of the sample collection on a separate sheet of paper. Samples were stored in the participants freezer until collected the following day. The tubes were then stored in the laboratory at -60 degrees Celsius. Melatonin concentrations in each tube were determined by radioimmunoassay technique at the Adelaide Research Assay Facility.

The onset of melatonin was estimated using a skewed baseline cosine function (SBCF) model fitted to the seven (melatonin concentration) data points using customized MATLAB software.

The SBCF model is given as  $Y(t) = b + (H/(2*(1-c))) * (\cos(t-\phi + v * \cos(t-\phi)) - c + |\cos(t-\phi + v * \cos(t-\phi)) - c|)$

where  $t$  = time (radians),  $b$  = baseline salivary melatonin,  $H$  = height of the amplitude above baseline,  $c$  = width,  $\phi$  = phase (radians), and  $v$  = skewness (radians).

DLMO in decimal time (corresponding to 1% above threshold melatonin concentration levels of 4.3pM) were obtained from the model fitting.

**Outcome measures:** DLMO decimal time

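### Water is encouraged before saliva collection, with no gap or drink record, while DLMO is read at a fixed melatonin concentration: an avoidable source of within-person noise in a primary outcome

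*Combined protocol and SAP*

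**What the plan says.** Protocol section 5.7, item 4, notes that chewing the swab may be inconvenient, particularly with a dry mouth, and adds: "participant are allowed/ encouraged to drink water beforehand to ease this inconvenience if it occurs". It does not say how long before the swab.

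Protocol section 5.5, item 4, describes collection: "Participants will provide salivary samples by chewing a cotton swab for 1min". On timing: "The participant will provide saliva every hour, starting 6 hrs prior to their sleep time", with one further sample about an hour after going to bed. The supplement (Dim Light Melatonin Onset) confirms seven tubes per time point, collected at home.

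The supplement states what is written down with the samples: "Participants were asked to write the time of the sample collection on a separate sheet of paper". It mentions no record of drinks.

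The supplement then fits a skewed baseline cosine curve with five parameters (b, H, c, phi, v) to the seven concentrations and reads the outcome from it: "DLMO in decimal time (corresponding to 1% above threshold melatonin concentration levels of 4.3pM) were obtained from the model fitting".

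The endpoint (supplement, Endpoints, Primary) is "Change from baseline to week 4 and week 6 in mean DLMO decimal time". Protocol section 2.2 also lists change in DLMO as primary.

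**The concern.** A fixed concentration threshold turns any error in measured concentration into an error in time. Water left in the mouth lowers the measured melatonin, so the fitted curve reaches the threshold later although the participant's circadian phase has not moved. The advice on comfort therefore works against the measurement it accompanies.

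Dry mouth, and with it drinking, may vary between people and between nights in one person. Unequal dilution between nights adds within-person scatter to a primary outcome. If drinking habits drift over the six weeks, it adds an apparent phase shift over time. Only collection times are recorded, so affected tubes cannot be identified afterwards, and a curve with five parameters on seven points (two residual degrees of freedom) has little capacity to absorb or reveal a bad tube.

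**Working it through.** The plan states no dilution, melatonin slope or DLMO error, so there is no figure of its own to reproduce. The minutes below are conditional.

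**Inputs from the documents.** Threshold: 4.3 x 1.01 = 4.343 pM. Seven tubes, five curve parameters, endpoint as change from baseline.

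**Assumed inputs.** Fraction of water in the sample, f: 10%, 20%, 30%. Local rise in melatonin, s: 3, 5, 10 pM/h.

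**Step 1: linear approximation.** A diluted sample reads 4.343 pM only when true melatonin is 4.343/(1 - f):

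- f = 0.1: 4.343/0.9 = 4.83 pM
- f = 0.2: 4.343/0.8 = 5.43 pM
- f = 0.3: 4.343/0.7 = 6.20 pM

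Delay in minutes = 60 x (4.343/(1 - f) - 4.343)/s:

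| Dilution | 3 pM/h | 5 pM/h | 10 pM/h |
|---|---|---|---|
| 10% | 9.7 | 5.8 | 2.9 |
| 20% | 21.7 | 13.0 | 6.5 |
| 30% | 37.2 | 22.3 | 11.2 |

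One of the nine cells exceeds 30 minutes.

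**Step 2: the plan's own curve.** With skewness v = 0, and t the time in hours before the peak, true melatonin on the rising limb is b + H(cos(2 pi t/24) - c)/(1 - c). If every tube is diluted by f, the crossing moves to where this equals 4.343/(1 - f). For assumed profiles with H = 20-40 pM (defined in the plan only as "height of the amplitude above baseline", with no value), b = 1 pM and c from -0.2 to 0.3, the delay is 2-7 min at 10% dilution, 5-15 min at 20% and 8-26 min at 30%. Over a wider assumed grid (H = 10-150 pM, b = 0.5-3 pM) it is 0.5-14, 1.2-32 and 2-55 min. At 20-30% dilution, more than 30 minutes needs a low, slow rise (H about 10-15 pM).

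**Step 3: refit to seven tubes.** The curve was refitted by least squares to the hourly schedule with c = 0.

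- All tubes diluted by 10/20/30%: about 8/17/31 min later at H = 15 pM; 0-8/4-12/11-16 min at H = 30 pM; -2 to 5/-2 to 3/1 to 10 min at H = 60 pM.
- One tube diluted by 30%: 17-27 min later if it is the tube one hour before bedtime, which lies next to the crossing in these profiles. For any other tube, between 7 min earlier and 5 min later, part of which is fit instability.

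**Step 4: effect on the endpoint.** Take a true change of -0.50 h, with b = 1 pM and c = 0:

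- 20% dilution at baseline and follow-up: read as -0.50 h, because the errors cancel.
- 0% then 20%: the follow-up crossing is delayed by 12.7 min (H = 20 pM) or 6.3 min (H = 40 pM), so the change reads -0.50 + 12.7/60 = -0.29 h or -0.50 + 6.3/60 = -0.40 h.
- 20% then 10%: read as -0.62 h or -0.56 h.

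Unequal dilution can thus shrink or exaggerate an individual change.

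**The case against.** Several objections are fair, and most of them limit the point.

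- **Dilution is not shown.** The sentence sits in a risk section, is conditional on discomfort, and gives no timing. Instructions are handed out with the Salivettes (protocol Table 1) and collection follows cited procedures; neither is visible here, and either might set a gap. This stands. What can be said is that the protocol and supplement are silent on the gap while encouraging the drink.
- **The endpoint is a change, and arms are randomised and blinded.** A reader might infer that the water advice biases the treatment comparison, or shifts the primary outcome by half an hour. The documents support neither. Equal dilution cancels, nothing makes drinking differ by arm, and the half-hour figure belongs to one extreme combination of assumptions. This stands in full.
- **A straight line is not the estimator.** Correct: tubes far from the crossing matter little, and with a high-amplitude rise the refitted shift can be near zero or slightly early. The refit still shows that a single diluted tube beside the crossing matters.
- **The threshold wording is loose.** If 1% referred to each person's own amplitude above their own baseline, uniform dilution would not move DLMO. The stated 4.3 pM favours the fixed reading.
- **The cost in power is unknown.** Protocol section 6.1 gives no SD or effect size for DLMO, so the loss cannot be computed.

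**Conclusion.** The point holds as a measurement weakness with a nearly free remedy. The plan encourages water before a sample whose concentration is compared with a fixed threshold, states no interval, and records nothing that would identify affected tubes. Where residual water reaches tubes near the crossing, that night's DLMO would usually be late, by about 3 to 37 minutes under the stated assumptions and 2 to 26 minutes for mid-range curves.

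The consequence for the trial is mainly extra within-person noise. A false within-group shift is also possible if drinking habits change between visits, and it would bear on the time-point comparisons planned in protocol section 6.2. A directional bias between arms is not supported. All minutes rest on assumed dilution and melatonin profiles and on the fixed-threshold reading.

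**What to change.** **Collection.** Replace the sentence in protocol section 5.7, and add the same rule to section 5.5 item 4 and the supplement's DLMO section: water may be taken straight after each hourly tube, but not within a fixed short interval before the next. Fifteen minutes is an example only, an assumed figure that the sponsor should set with the assay laboratory. Keep the one-minute chew unchanged, since lengthening it for dry mouths would make collection vary in the very participants at issue.

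**Record.** Add a tick box for a drink within that interval to the existing saliva time sheet. The hourly reminder in section 5.5 can carry the instruction.

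**Sensitivity analysis.** If one tube is ticked on a night, refit DLMO without it (six points, five parameters). If two or more are ticked, flag that night's DLMO and repeat the mixed model without it: dropping two tubes leaves five points for five parameters, and dropping three leaves fewer points than parameters.

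**Samples already collected.** Report the absence of a drink record as a limitation.

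**Cost.** One sentence, one tick box and one sensitivity analysis. The downside is slight discomfort for participants with a dry mouth, eased because tubes are an hour apart.

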#### 4.3. Recruitment strategies, timeframe

We will allow an 18 months recruitment period. Recruitment strategies include approaching participants from the Movement Neuroscience group at QUT and our previous studies in PD if they have consented to be approached. It will further include approaching participants from Dance Parkinson's classes held at QUT (once a week), and media advertising (QUT media). One of the team members is a neurologist at the Mater hospital and he will provide information/flyers about the trial, however will not recruit or consent participants to avoid pressure and coercion. He will also contact patients from his clinical practise and obtain consent to pass their contact details to the QUT research team to discuss participation in the study. We anticipate to achieve the required number of participants (n = 60) through the above-mentioned avenues as previously shown in our studies. However, if required, will also expand our recruitment strategy through presentation of the clinical trial information by researchers, flyers provided to Parkinson's support groups, the Men's Shed community groups, and older people's community centres.

All resources are available at QUT and the team members have long-standing experience in all aspects of the protocols. We therefore do not foresee challenges in recruitment within this timeframe, however we can extend the timeline of recruitment if required. To retain participants throughout the study period (6 weeks) we will closely monitor engagement (4 home visits as well as 3 laboratory visits and frequent text message or calls during the intervention period). Our statistical methods also account for a 15 % drop out rate in case some of the participants cannot be retained.

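### The only symptom procedure visible in the protocol waits for a complaint and states no recording step, so the plan supports no adverse-event incidence by arm

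*Combined protocol and SAP*

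**What the plan says.** Protocol section 5.7 is the only safety section. It makes these statements:

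- The general risk statement is that "there is a low probability of slight inconvenience, but no harm to the participant associated with the research".
- Item 6, on motor testing, says "There is a minor risk of a falling when testing gait and balance motor functions in participants with PD", with research staff closely monitoring the assessments.
- Item 7, on light therapy, says that bright light may cause brief, mild headache and eye strain. It then quotes a meta-analysis in bipolar disorder, introduced by "The most common adverse effects were very rare and are listed below". Eleven rates follow. The first three are "headache = 4.7% (7/148"), "sleep disturbance = 1.4% (2/148") and "insomnia = 0.68% (1/148").
- The response to symptoms is: "If a participant complains about any of the above symptoms during or after light therapy the research team will discuss them with the participants". The team may advise withdrawal, depending on severity.

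Table 1 in section 5.2 lists no adverse-event question at any visit. Neither the outcome list in section 2.2 nor the Endpoints page of the supplement contains a harm. The analysis text in section 6.2 and in the Supplementary Methods covers only the primary, secondary and exploratory outcomes, light exposure and melanopsin function.

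Section 4.3 promises home visits, laboratory visits and "frequent text message or calls during the intervention period", with the stated purpose of monitoring engagement. Section 5.2 refers to a safety section of the ethics application (HREA 7.7), which is not among the documents.

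**The concern.** A rule that starts with a complaint records what participants choose to mention, and a rule tied to a list gives no instruction for anything off the list. A fall at home or a visual change other than eye strain is not listed. Section 5.7 also stops at a discussion. It does not say that the complaint is written down, graded or counted.

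The light box is custom-built, stands about 30 cm from the participant and is used for 30 minutes a day at home. Acuity, slit lamp, fundus and OCT examinations are described only for screening. At weeks 4 and 6 the only eye-related measurement is pupillography. If nothing is asked and nothing is tabulated, the trial report will have no numerator or denominator for harms in either arm, and a lack of complaints will carry little information.

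**Working it through.** **1. Where could an adverse event enter the data?**

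- *Visits (Table 1):* questionnaires, pupillography, motor tests, saliva, polysomnography, actigraphy and diary. There is no adverse-event item.
- *Outcomes (section 2.2; supplement, Endpoints):* no harm at any tier.
- *Analysis (section 6.2; Supplementary Methods):* mixed models for the outcomes, and ANOVA for light exposure and baseline melanopsin function. There is no harms table.
- *Section 5.7:* discussion on complaint, with no recording step.
- *Overlapping instruments:* PSQI, PDSS, ESS, BDI-II and MDS-UPDRS at the three time points, and a six-week sleep diary. The scales are analysed as mean scores. No analysis is stated for the diary.

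**2. Reproduce the protocol's rates.** 7/148 = 4.73%, 2/148 = 1.35%, 1/148 = 0.68% and 1/132 = 0.76%. All 11 stated figures agree. Headache is about 1 in 21 (148/7 = 21.1), with an exact 95% interval of 1.9% to 9.5%. Sleep disturbance is 1 in 74. The other nine are single events.

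**3. Illustration in this trial.** Inputs: 60 participants (section 6.1) and the cited headache rate. The allocation ratio is not stated, so 30 per arm is assumed.

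- Expected headaches: 60 × 0.0473 = 2.8 in total; 30 × 0.0473 = 1.4 per arm.
- Chance of at least one in 60: 1 − (1 − 0.0473)^60 = 0.945.
- Chance of at least one in 30: 1 − (1 − 0.0473)^30 = 0.766.
- All listed events, assuming no overlap between them: 60 × (14/148 + 4/132) = 60 × 0.125 = 7.5.
- Sleep items (sleep disturbance, insomnia, nightmares), which the sleep scales touch: 60 × (3/148 + 1/132) = 1.7 of those 7.5.

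**4. Effect of relying on volunteered reports.** The documents give no reporting fraction, so a range is assumed. If half of headaches are volunteered, the chance of hearing of at least one in an arm of 30 is 1 − (1 − 0.0236)^30 = 0.51. If a quarter are volunteered, it is 1 − (1 − 0.0118)^30 = 0.30.

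**5. What complete capture could show.**

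- Zero events in 30 leaves a one-sided 95% upper limit of 1 − 0.05^(1/30) = 9.5%, and a two-sided exact limit of 1 − 0.025^(1/30) = 11.6%.
- With 30 per arm and a two-sided 5% level, power to separate 4.7% from 10%, 20% or 30% is 12%, 43% or 75%.
- A comparison of 4.7% with 20% at 80% power needs 72 per arm.

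The data would support description with intervals, not a test.

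**The case against.** **Other capture exists.** The sleep and mood scales and the diary are scheduled, so it would be wrong to say that harms are captured only by complaint. This stands for the sleep items and in part for mood. It does not extend to headache, eye strain, nausea or palpitation, which no instrument is described as recording, and a mean score gives no count of affected participants.

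**The procedure may lie elsewhere.** The ethics application's safety section may contain recording rules. That cannot be excluded. The pointer to it, however, sits in a sentence about light output levels, and the visible analysis plan would still have no harms table.

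**The section 5.7 sentence is a response rule for one item.** It says how the team reacts to light-therapy symptoms and does not forbid noting other events. Motor tests are supervised, light-box failure is to be reported, and contact is frequent. This is fair, but none of it is described as recording adverse events.

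**The cited rates are weak evidence.** They come from bipolar disorder, and the protocol sets no threshold for rarity. Ten of the 11 are 1.4% or less. Only headache clearly does not fit the label.

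**Stronger readings that the documents do not support.**

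- A reader might infer that the trial set out to compare the tolerability of the two lights and fails to do so. No aim or outcome says this.
- A reader might conclude that nothing at all could be said about tolerability. Withdrawals and the scales by arm give indirect evidence.
- A reader might take the missing data in Table S1 as a sign of intolerance. At week 4, PDQ-39 is present for 26 of 30 Enhanced Mel and 27 of 27 Day Mel participants (Fisher p = 0.11), and MDS-UPDRS for 17 of 30 and 24 of 27 (p = 0.009). No reasons are given. At least 26 − 17 = 9 Enhanced Mel participants without MDS-UPDRS did return a PDQ-39, so that gap is not simply drop-out. Intolerance can be neither inferred nor ruled out.

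**Conclusion.** The point holds in this form: the visible plan has a passive symptom rule tied to a list, no stated recording step, no adverse-event question at any visit and no harms analysis. It therefore supports no adverse-event incidence by arm. This should be improved because the change is cheap. It does not affect the efficacy analysis.

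The size is illustrative: about 2.8 headaches in 60 participants, a 95% chance of at least one, and 77% in an arm of 30. These figures assume that a bipolar-disorder rate transfers to Parkinson's disease and that the arms are equal. The conclusion also assumes that the unseen ethics section adds no recording and tabulation rule.

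A secondary wording point: the general statement in section 5.7 that the research carries no harm conflicts with the fall risk, headache and eye strain named in the same section, and the rarity label does not fit headache at about 1 in 21. These passages should be reconciled.

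**What to change.** At the existing week 2 home visit and the week 4 and week 6 laboratory visits, have blinded staff ask one open adverse-event question. Follow it with a short checklist covering the symptoms listed in section 5.7, falls and visual change. Record onset, severity, action taken and resolution, and do not limit recording to listed symptoms.

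Add to section 6.2 a table of participants with each event by randomised arm, with exact 95% intervals. It should be descriptive, without a test, and should state that zero events in 30 still allows a true rate of about 10% to 12%.

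Leave the existing text on discussing symptoms and advising withdrawal as it is. The change concerns recording and reporting only.

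The cost is a one-page form, about five minutes at each of three visits already scheduled, and one table. The downside is that prompted questions raise the count of minor events in both arms.
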